### Parent’s diet

Parents’ dietary intake will be assessed using a validated Food Frequency Questionnaire, *The Cancer Council’s Dietary Questionnaire for Epidemiological Studies (Version 3.1)* when child is 3, 18 and 36 months of age [52].

### Parent’s physical activity and television viewing

Parents will report their physical activity behaviours using the validated *Active Australia Survey* [53] at 3, 18, 36 months. Parents will also report the total time they spend watching television during their leisure-time in a typical week [54].

### Home food environment

A range of home food environment variables will be assessed at 3, 18 and 36 months. Aspects of *nutrition knowledge* focused around nutrition targets of the intervention will be assessed using modified subscales of the validated *Nutrition Knowledge Questionnaire* [55, 56], Parent Feeding Style will be assessed using a modified version of *the Comprehensive Feeding Practices Questionnaire* [57]. Covert restriction will be assessed using a validated subscale [58].

Opportunities for *modelling of healthy eating* (e.g. sharing family meals) and *home food availability* will be measured using previously established tools [59].

Parental confidence regarding promoting healthy eating (and reducing sedentary time/promoting physical activity) will be assessed using established tools [60].

### Home physical activity and sedentary environment

Parents will be asked general questions relating to their knowledge about physical activity in early childhood, their interactions with their child around physical activity and an audit checklist on the physical activity and sedentary home environment at 3, 18, 36 months.

### Economic evaluation

#### Health service use

Exposure to the InFANT Extend Program may have implications for families’ use of the broader health system if the information provided through the program reduces parent’s help-seeking behaviour elsewhere. It is therefore important to monitor use of relevant health services, especially MCHn visits as the primary health provider in this population. Parents will be asked to report the use of services related to their infant’s or their own weight, diet/eating behaviours or physical activity in order to capture any differential use of health and other services associated with the intervention. Parents will be asked to report specifically on their use of MCHns, and more generally on a broad range of services. In each case, parents will be asked to report the number of occasions of service use and, where applicable, any financial cost. The investment of resources involved in reported use of health services will be costed using established unit costs for wages, services and material costs in Australian dollars.

### Statistical analyses

Intervention effects will be assessed based on intention to treat principles and taking into account the cluster-based sampling design. Generalized Estimating Equations [61] using the xtgee function in Stata, will be used to fit longitudinal regression models enabling comparison of primary outcome variables between intervention and control groups, adjusted for baseline values where appropriate (infants were not consuming foods nor mobile at baseline, i.e. 3 months of age, hence adjustment for diet or physical activity variables is not possible).

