### Study participants and recruitment

The recruitment process for the InFANT Extend Program will largely replicate that used in the original Melbourne InFANT Program [24, 35]. An important exception relates to the local government area (LGA) recruitment strategy. To seek to address the over representation of university educated women in the Melbourne InFANT Program [24] seven relatively disadvantaged Victorian LGAs will be purposively recruited. These LGAs will selected by the group level variable *Index for Socio Economic Disadvantage* (IRSD) [37] such that all will be in the lowest tertile of disadvantage (i.e. most disadvantaged). It is important to note that there will be distinct areas of greater and lesser socioeconomic advantage within each LGA and these are indicated by the IRSD of postcode regions within each LGA. For practical reasons, each LGA will sit within a 75km radius of the research center (Geelong, Victoria, Australia).

Eighty percent of eligible first-time parents’ groups (rounded to next even number to ensure equal within LGA allocation to control and intervention groups) within each of these LGAs will be randomly selected and approached by research staff for recruitment during one of the standard nurse-facilitated group sessions. Individual parents will be eligible to participate if they give informed written consent, are first-time parents and are literate in English. Infants with chronic health problems likely to influence height, weight, levels of physical activity or eating habits will be excluded from analyses but will be permitted to participate in the program.

Parent groups will be eligible if eight or more parents choose to enroll in the study. To facilitate inclusion of participants experiencing disadvantage, groups commencing in MCH centres considered relatively socioeconomically disadvantaged (as determined by the post code of the region within each LGA), will be eligible if six or more parents enroll. When first-time parents’ groups decline to participate, the next randomly selected group within the LGA will be approached. Non-consenting parents within participating groups will be permitted to attend the intervention sessions, but will not be required to provide data or be contacted by the research team in any other way.

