Randomization of first-time parents’ groups (clusters) to intervention or control will occur after recruitment to avoid selection bias [38]. Randomization (stratified by LGA) will be conducted by an independent statistician. While parents will not be blinded to allocation, they will not be informed of the study aims or hypotheses and the recruiting emphasis will focus on promoting healthy eating and active play from the start of life. Staff measuring height and weight will not be blinded to intervention status as they will deliver the intervention, however, data entry and analyses will be conducted with staff blinded to participant’s group allocation.

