### Sample size

#### Power and sample size

Child weight and waist circumference are the primary outcome measures for this study and considered the most difficult outcomes to change. Secondary aims of this intervention are to increase children’s fruit and vegetable consumption and time spent physically active, and to decrease consumption of sweetened drinks and time spent sedentary.

Australian national data [39] report an average weight and waist circumference in 3-year old children of 16.4kg (SD = 2.2kg), and 51.1cm (SD = 3.8cm) respectively [39]. Further, these data report that at this age Australian children consume an average of 85g (SD = 82g) of vegetables (not including potato), 202g (SD = 129g) of fruit and 78mL (SD = 121mL) of sweetened drinks daily. Additionally this group is reported to spend an average of 117min (SD = 30min) being active and 662min (SD = 71min) being sedentary daily [40].

To detect a 5% difference in weight between groups at age three (reducing average weight in the intervention group by approximately 1kg), with Type I and Type II errors of 5% and 20% respectively, the number of subjects required is given by:$$ \mathrm{N}\ \left(\mathrm{number}\ \mathrm{of}\ \mathrm{subjects}\right) = 32/\mathrm{E}\mathrm{S}\ {\left(\mathrm{Effect}\ \mathrm{S}\mathrm{ize}\right)}^2 $$$$ \mathrm{E}\mathrm{S} = \left(\mathrm{mean}\ \mathrm{x}\ \%\ \mathrm{meaningful}\ \mathrm{difference}\right)/\mathrm{standard}\ \mathrm{deviation} $$$$ \mathrm{So},\ \mathrm{N} = 32/0.382 = 223 $$

This sample size will also allow us to detect differences of: 4% in BMI (i.e. 0.66kg/m^2^), 3% in waist circumference (i.e. 1.5cm), 36% in vegetable consumption (i.e. 31g, equivalent to approximately ½ a serve/day); 24% in fruit consumption (i.e. 49g, equivalent to approximately 1/3 of a serve/day); 60% in sweetened drink consumption (i.e. 47mL/day); 10% in active time (i.e. 12min/day) and 4% in sedentary time (i.e. 26min/day).

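### Randomisation is stratified by LGA, but the stated adjustment does not include LGA; if LGAs differ on weight or waist, the analysis gives away precision

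*Protocol article*

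**What the plan says.** The design is set out in the protocol article under Study participants and recruitment. There, "seven relatively disadvantaged Victorian LGAs will be purposively recruited", and parents' groups are sampled within each. The number of groups per LGA is "rounded to next even number to ensure equal within LGA allocation to control and intervention groups". The same section states: "Randomization (stratified by LGA) will be conducted by an independent statistician".

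The analysis is set out under Statistical analyses: intention to treat, GEE fitted in Stata, "taking into account the cluster-based sampling design", and models "enabling comparison of primary outcome variables between intervention and control groups, adjusted for baseline values where appropriate". That paragraph explains why baseline diet and activity values cannot serve as covariates. It neither names LGA as a model term nor excludes it.

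Under Child's anthropometry, waist circumference, one of the two primary outcomes, is measured at 18 and 36 months only. It therefore has no 3-month value to adjust for.

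**The concern.** When groups are split equally between arms inside each LGA, any difference between LGAs contributes equally to both arms and drops out of the estimated arm difference. It does not drop out of the estimated standard error unless the model knows about LGA. A model that omits the stratum counts the LGA spread as noise, although the design has already removed that noise from the comparison. The result is a confidence interval that is too wide and a test that rejects less often than its nominal level.

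Allowing for clustering does not cure this. Clustering by parents' group handles the correlation of children within a group. Stratification concerns what different groups in the same LGA share, and a GEE clustered on groups treats those groups as independent. Baseline adjustment could absorb part of the LGA difference for weight. For waist circumference there is no baseline value of the outcome to do so.

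At stake is precision that the stratification may already have bought. The comparison itself is not biased.

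**Working it through.** **The plan's own figures (Power and sample size).** The calculation is made "with Type I and Type II errors of 5% and 20% respectively". Mean weight is 16.4 kg with SD 2.2 kg, so a 5% difference is 0.82 kg and the effect size is 0.82/2.2 = 0.373, used as 0.38. Then 32/0.38² = 221.6, against 223 stated, and 223 × 1.8/0.75 = 535.2, against 535 stated. The 540 recruited children give 540 × 0.75/1.8 = 225 effective children. Power is then 81.3% at an effect size of 0.38, or 79.8% at 0.373. The formula contains no gain from stratification.

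**Inputs for the check.**
- From the article: 30 groups per arm, 9 children per group, attrition 25%, ICC 0.10, seven LGAs.
- Derived: analysed children per group m = 9 × 0.75 = 6.75.
- Assumed, because the article does not give it: the share *s* of the between-group variance that lies between LGAs, taken as 0%, 10%, 25% and 50%. Exact balance within each LGA is also assumed, with no variance explained by baseline values.

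**Formulas, in SD units.**
- Variance of a group mean, LGA left in: 0.10 + 0.90/6.75 = 0.2333.
- Variance of a group mean, LGA removed: 0.2333 − 0.10*s*.
- SE reported without LGA: √(2/30 × 0.2333) = 0.1247.
- True SE, which is also the SE with LGA in the model: √(2/30 × (0.2333 − 0.10*s*)).
- Ratio r = reported SE/true SE.
- Type I error without LGA: 2[1 − Φ(1.96r)].
- Power without LGA: Φ(0.373/true SE − 1.96r). Power with LGA: Φ(0.373/true SE − 1.96).

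**Worked at s = 50%.** The variance is 0.1833 and the true SE 0.1106, so r = 0.1247/0.1106 = 1.128. Type I error is 2[1 − Φ(2.211)] = 2.7%. Power is Φ(3.371 − 2.211) = 87.7% without LGA and Φ(3.371 − 1.96) = 92.1% with it.

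| LGA share | SE ratio | Type I error without LGA | Power without LGA | Power with LGA | Points forgone |
|---|---|---|---|---|---|
| 0% | 1.000 | 5.0% | 84.8% | 84.8% | 0 |
| 10% | 1.022 | 4.5% | 85.3% | 86.3% | 1.0 |
| 25% | 1.058 | 3.8% | 86.2% | 88.6% | 2.4 |
| 50% | 1.128 | 2.7% | 87.7% | 92.1% | 4.4 |

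Power starts above 80% because the design effect at 6.75 children per group is 1 + 5.75 × 0.1 = 1.575, not 1.8.

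**Sensitivity.** With the plan's own design effect of 1.8 and effect size of 0.38, the SE ratios are 1.000, 1.026, 1.069 and 1.155. The power forgone is 0, 1.3, 3.2 and 6.0 points.

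**Simulation.** I simulated group means for 60 groups in LGAs of 8, 8, 8, 8, 8, 10 and 10 groups, with 8,000 replicates under no effect (Monte Carlo error about 0.3 points or less) and 4,000 at effect size 0.373. At a 50% share, a group-level t-test had type I error 3.1% without LGA and 5.0% with it; power was 87.6% and 91.8%. At a 0% share the two analyses did not differ (5.1% each; power 84.4% each).

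An uncorrected robust z-test behaved differently. At shares of 0%, 10%, 25% and 50% its type I error was 6.1%, 5.5%, 4.5% and 3.7% without LGA, and 8.0%, 7.5%, 7.0% and 7.4% with it.

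**The case against.** The strongest reply is that this is detail for the statistical analysis plan. The source is a condensed article, its analysis section is two sentences long, and the full covariate list may stand in a document that is not shown. A reader might infer that the trial will definitely leave LGA out. The article does not support that, since it never says that baseline values are the only adjustment. What remains is that the paragraph is not silent on adjustment. It gives a rule and discusses its limits, and that rule, followed as written, omits the factor on which randomisation was stratified.

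A second reply is that LGAs may hardly differ. All seven come from the most disadvantaged third, all lie within 75 km of one centre, and the article notes marked socioeconomic variation inside each LGA. This stands: a small share is plausible, and at zero nothing is lost.

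A third reply is that conservatism is not guaranteed for the planned GEE, because the type of standard error is not stated. This also stands. With an uncorrected robust z-test and an LGA share of 0% to 10%, the simulated test without LGA was slightly liberal, and adding LGA alone made error control worse. That is a small-sample effect separate from the stratification effect, and it is why the correction must accompany the LGA term.

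**Conclusion.** The point holds as a conditional and modest one. The design is stratified by LGA with equal allocation, and the stated adjustment does not carry the stratum into the model. If LGAs differ on the outcome, the standard error is overstated by about 2%, 6% or 13% at LGA shares of 10%, 25% or 50%. About 1, 2 to 3 or 4 points of power are then forgone compared with an LGA-adjusted analysis, or up to 6 with the plan's own design effect. The mechanism is secure. The size is not, because it rests on an LGA share that the article does not give.

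Two stronger readings are not supported. A reader might infer that the trial falls below its planned power. It does not: in every scenario the analysis without LGA stays at about 80% or above. A reader might also infer that omitting LGA raises the risk of a false positive result. The effect of the omission runs the other way.

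**What to change.** Add to Statistical analyses, for weight and waist circumference:

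> The GEE models for the primary outcomes include LGA (the randomisation stratum, seven levels) as a fixed effect. The first-time parents' group is the clustering unit, and standard errors are corrected for the small number of clusters.

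If the analysis plan already says this, a cross-reference is enough. The two parts should be adopted together, given the 7% to 8% type I error found for LGA with an uncorrected robust test.

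The cost is 6 degrees of freedom: in a group-level analysis, 60 − 2 = 58 become 60 − 8 = 52. No new data are needed. If LGAs do not differ there is no gain, and the simulated loss of power at a zero share was negligible. The analyst should confirm that the chosen software routine offers the small-sample correction.

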As this study will randomize by first-time parents groups, we need to take account of within-group clustering and increase our sample size according to the design effect/inflation factor (DEFF). The design effect is given by: DEFF = 1 + [(n-1) x ICC], where n is the number of people in each cluster and the ICC is the intra-class coefficient. Based on our previous experience working with first-time parents groups, we estimate that each cluster contains an average of nine mother-infant pairs, and the ICC is estimated to be 0.1 (based on data from the Melbourne InFANT Program), thus the design effect is 1.8. We will also adjust our sample size to account for estimated attrition over the three years of the study (<25%).

Therefore, our final sample size is: (223 x 1.8) / 0.75 = 535. To achieve an equal number of groups in each arm of the trial (mean number of participants in groups = 9), we will aim to recruit 540 participants from a total of 60 first-time parents’ groups (30 groups and 270 participants in each arm of the trial).

The CONSORT flow diagram is outlined in Fig. 1.

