### Data collection

#### Measures

As outlined in Table 2, parent and infant data will be collected at 3, 18 and 36 months. Standard demographic and socio-economic information will be collected by parental report at baseline (3 months). Additional measures to be collected are detailed below.

**Table 2 Tab2:** Measures and time-frame for the study

Intervention timeline - year		1	2				3	4
Measures		Infant age						
		3 months	6 months	9 months	12 months	15 months	18 months	36 months
Dietary intake	Parent Child	✓ ✓		✓*			✓ ✓	✓ ✓
Sedentary behaviour	Parent Child	✓		✓ ✓			✓ ✓	✓ ✓
Physical activity	Parent Child	✓		✓ ✓			✓ ✓	✓ ✓
Family food environment	Parent	✓		✓			✓	✓
Family physical activity & sedentary environment	Parent	✓		✓			✓	✓
Demographic data	Parent	✓						
Anthropometric data	Parent Child	✓ ✓		✓ ✓			✓ ✓	✓ ✓

*Modified FFQ

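### As written, the waist model would have no baseline size covariate and the weight model only the child's own 3-month weight, although child and parent anthropometry are scheduled at 3 months: an optional gain in precision

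*Protocol article*

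**What the plan says.** The Statistical analyses section fits longitudinal GEE models that allow for clustering, "enabling comparison of primary outcome variables between intervention and control groups, adjusted for baseline values where appropriate". A parenthesis adds that infants were neither eating foods nor mobile at 3 months, so diet and physical activity cannot be adjusted for. No covariate is named.

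Table 2 (Data collection, Measures) has a row for "Anthropometric data" with ticks for parent and child at 3 months, without distinction by arm. It does not say which parent measurements are taken.

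Under Child's anthropometry, waist is measured at 18 and 36 months only. Weight and waist are the two primary outcomes (Primary outcomes; Power and sample size).

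The sample size section gives means and SDs of "16.4kg (SD = 2.2kg), and 51.1cm (SD = 3.8cm) respectively" from national data. It makes no allowance for covariates.

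**The concern.** The phrase about baseline values is loose, but its parenthesis gives it a meaning. A missing 3-month value makes adjustment impossible only if the adjustment intended is for the outcome's own earlier value. Read that way, the two primary outcomes are treated differently. Weight is adjusted for 3-month weight. Waist has no 3-month value, so its model has nothing to adjust for. The section explains the missing baseline for diet and activity but not for waist.

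The 3-month visit nevertheless yields size measurements on both child and parent. To the extent that these predict size at 36 months, leaving them out keeps explainable between-child variance in the error term and widens the confidence intervals for the primary outcomes. Waist has most to gain, because it starts with no size covariate. What is at stake is precision: randomization protects the comparison of means whether or not the covariates are used.

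**Working it through.** **1. Reproduce the plan's figure.** Inputs from Power and sample size:
- errors: "with Type I and Type II errors of 5% and 20% respectively";
- target: "To detect a 5% difference in weight between groups at age three", that is 0.05 × 16.4 = 0.82 kg;
- SD for weight: 2.2 kg;
- clustering: "each cluster contains an average of nine mother-infant pairs" and "the ICC is estimated to be 0.1";
- attrition: 25%.

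ES = 0.82 / 2.2 = 0.373, which the plan takes as 0.38. N = 32 / 0.38² = 221.6, against the stated 223. (The printed divisor 0.382 is read as 0.38 squared with its superscript lost.) DEFF = 1 + 8 × 0.1 = 1.8, and 223 × 1.8 / 0.75 = 535.2, against the stated 535. The figure reproduces, and it uses raw SDs with no covariate.

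**2. Which baseline values exist for the primary outcomes.**

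| Outcome | Own 3-month value | Other size data at 3 months |
|---|---|---|
| Weight | Yes | Child length; parent anthropometry |
| Waist | No (first measured at 18 months) | Child weight and length; parent anthropometry |

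The 18-month waist cannot stand in as a baseline, because it follows the group-delivered part of the intervention (3 to 18 months).

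**3. Size of the gain.** Let R² be the share of the remaining outcome variance that the added covariates explain. The documents give no value, so 3%, 5% and 10% are assumptions. Adding the covariates multiplies the residual variance by (1 − R²), which is equivalent to multiplying the sample by 1/(1 − R²): 1.031, 1.053 and 1.111, or about 3%, 5% and 11% more children. This ratio does not depend on the starting variance. It assumes that the ICC is unchanged.

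Power = Φ( (d/SD) × √(223/(1 − R²)) / 2 − 1.96 ), where 223 is the plan's number before inflation for clustering and attrition.

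| Assumed R² | Weight, d = 0.82 kg, SD 2.2 | Waist, d = 1.5 cm, SD 3.8 |
|---|---|---|
| 0 | Φ(2.783 − 1.96) = 79.5% | Φ(2.947 − 1.96) = 83.8% |
| 3% | Φ(2.826 − 1.96) = 80.7% | Φ(2.993 − 1.96) = 84.9% |
| 5% | Φ(2.855 − 1.96) = 81.5% | Φ(3.024 − 1.96) = 85.6% |
| 10% | Φ(2.934 − 1.96) = 83.5% | Φ(3.107 − 1.96) = 87.4% |

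The waist difference is the plan's own: "3% in waist circumference (i.e. 1.5cm".

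**4. A wider range.** Take the effective number implied by the recruitment target, 540 × 0.75 / 1.8 = 225, and an assumed correlation r of 0.1 to 0.4 (R² = r², 1% to 16%). Power for weight goes from 79.8% to between 80.2% and 86.2%. Power for waist goes from 84.1% to between 84.5% and 89.8%. The 535 to be recruited would correspond to between 530 (535 × 0.99) and 449 (535 × 0.84).

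**5. A limit of these figures.** The weight column starts from the raw SD. The planned model already includes 3-month weight, so its true starting power is probably above 79.5% and the gain in percentage points would differ. The 3% to 11% equivalent in children is unaffected.

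**The case against.** The strongest objection is that this is one sentence in a condensed article. It does not close the list of covariates, and a full list commonly sits in an analysis plan that is not shown. That stands: the absence of a list is no fault. What remains is that the sentence ties adjustment to the existence of the outcome's own 3-month value, and this rule leaves waist with nothing.

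A second objection is that nothing here is wrong. Leaving out a prognostic covariate in a randomized comparison of means costs precision, not validity, and the sample size takes no credit for adjustment. That also stands, and it sets the weight of the point.

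Third, the documents give no figure linking parental size to child size, and Table 2 does not say whether parental height and BMI are among the measures. Both are true. The gain is therefore shown as an assumed range, and the parental covariates are conditional on what is measured.

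Several stronger readings are tempting but unsupported:
- That both primary models adjust for the outcome's own baseline and nothing else. This is not so for waist, which has no baseline; for weight, the wording excludes no other covariate.
- That the trial is biased or underpowered for this reason. The stated size reproduces without any covariate.
- That adjusting for parental size would also lower the ICC. The protocol takes 0.1 from the earlier trial and says nothing about what lies behind it.

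**Conclusion.** The point holds as an optional improvement. Under the plan as worded, the waist model has no baseline size covariate and the weight model has only the child's own 3-month weight, while further size data on child and parent are scheduled at the same visit. With an assumed partial R² of 3% to 10%, using them is worth about 3% to 11% more children, or roughly 1 to 4 points of power for each primary outcome reckoned from unadjusted SDs. No stated figure is wrong, no bias is involved, and the true gain is unknown because the documents give no correlation. The conclusion rests on reading the parenthesis as defining baseline values, and on the 3-month parent measurements including some measure of size.

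**What to change.** Add one sentence to Statistical analyses: the weight and waist models both include the child's 3-month weight, the waist model also includes 3-month length, and both include the participating parent's size at 3 months (BMI and height, if those are the measures taken). Use 3-month parental values only, since later ones could be affected by the programme. Fill missing baseline covariates by a simple imputation so that no child is dropped. State in the same place that waist has no 3-month value.

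The cost is one sentence, a little more analysis work and a few imputed covariate values. No extra data collection is needed, because the measurements are already in Table 2. The choice should be fixed before outcome data are examined by arm.

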### Measurement of physical activity and sedentary behaviours

Seven days of objectively assessed physical activity data will be collected using accelerometers at 18 and 36 months. At this time children will be fitted with an ActiGraph accelerometer which they will wear for eight consecutive days (which will capture weekday and weekend day activity and sedentary patterns) [44]. ActiGraph monitors are small, light and unobtrusive and are worn on a belt around the waist. This methodology was successfully employed during the original InFANT Program intervention when children were aged approximately 19 months. ActiGraph counts correlate (up to r = 0.70) with energy expenditure estimated by direct observation and doubly-labelled water respectively, among 3–5 year old children [45, 46] and correlate highly (r = 0.87) with energy expenditure estimated by indirect calorimetry among children [47]. Counts will be recorded at 15-s epochs to accurately capture the sporadic and intermittent activity patterns of young children. Data will be downloaded and then reduced to total counts/day, minutes/day and percentage of time spent sedentary, and in light-, moderate- and vigorous-intensity physical activity using age-appropriate cut points [48]. In addition, indirect measures of children’s physical activity will be assessed by parental report including: parental engagement in physically active play and the number of hours the child typically spends playing outdoors on weekdays and weekend days.

In addition, parents will be asked to indicate how much time (hours/min) their child usually spends watching television/DVD and playing electronic games on a typical weekday (Monday-Friday) and on a typical weekend day (Saturday and Sunday) and to estimate the amount of time spent in situations that restrict movement (e.g. stroller, playpen) at 3, 9, 18 and 36 months. Test-retest reliability of these items in a previous study ranged from ICC = 0.5–0.9 [49]. Parental reports of their child’s “usual” TV viewing has been shown to correlate with both videotaped observations of the child’s TV viewing [50] and with parental diaries of viewing [51].

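### Baseline adjustment is called impossible for diet and activity outcomes, which is right only for the child's own 3-month values; prognostic parent and home measures are scheduled at 3 months, and some precision is forgone

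*Protocol article*

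**What the plan says.** The Statistical analyses section fits longitudinal GEE models by intention to treat, allowing for clustering, with adjustment for baseline values where this is suitable. A parenthesis then makes an exception. Infants at 3 months were neither eating foods nor mobile, "hence adjustment for diet or physical activity variables is not possible".

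The measurement sections schedule several related quantities at 3 months, none of them limited to one arm:

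- Parent diet, by a validated food frequency questionnaire, "when child is 3, 18 and 36 months of age" (Parent's diet).
- Parent physical activity, by a validated survey, "at 3, 18, 36 months" (Parent's physical activity and television viewing).
- "A range of home food environment variables will be assessed at 3, 18 and 36 months" (Home food environment), with the same time points for the home activity and sedentary environment in the section that follows.
- The child's own television, electronic game and restraint time, by parent report, "at 3, 9, 18 and 36 months" (Measurement of physical activity and sedentary behaviours).

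The child food frequency questionnaire and child accelerometry are described only at 18 and 36 months.

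**The concern.** The reason given is narrower than the conclusion drawn from it. That an infant has no diet of foods and no mobility at 3 months means there is no own-baseline value to put in the model. It does not mean that no baseline variable can be used. The Background names parental knowledge, feeding style, modelling and what is made available at home as the routes by which parents shape children's eating and activity. The 3-month parent and home measures are therefore natural candidates as prognostic covariates.

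At stake is the width of the intervals for the secondary outcomes on fruit, vegetables, sweetened drinks, snacks and physical activity. There is also a practical risk. An analysis plan that follows the published sentence forgoes these covariates, while one that departs from it may have its covariate choice challenged as made after the fact.

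**Working it through.** **1. What is available at 3 months**

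| Outcome | Own 3-month value described? | Related 3-month measure |
|---|---|---|
| Child diet (FFQ) | No, 18 and 36 months only | Parent diet; home food environment |
| Child activity and sedentary time (accelerometer) | No, 18 and 36 months only | Parent activity; home activity and sedentary environment |
| Child television viewing | Yes, parent report | Own value |

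The exception is correct for the first two rows if it means own-baseline values. It does not mention the third row.

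**2. Does the plan's power rely on adjustment?**

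Inputs from Power and sample size: "To detect a 5% difference in weight between groups at age three", "with Type I and Type II errors of 5% and 20% respectively", mean weight 16.4 kg, SD 2.2 kg; cluster size 9, ICC 0.1, attrition 25%.

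- Effect size = 0.05 × 16.4 / 2.2 = 0.82 / 2.2 = 0.373, which the protocol takes as 0.38.
- N = 32 / 0.38² = 222; a direct two-sample calculation gives 2 × 113 = 226. The protocol states 223, so it reproduces closely.
- Design effect = 1 + 8 × 0.1 = 1.8, and 223 × 1.8 / 0.75 = 535.2. The protocol states 535.

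With N = 223 the detectable standardised difference is √(32/223) = 0.379. Multiplied by the protocol's SDs:

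| Outcome | SD | Computed | Stated |
|---|---|---|---|
| Vegetables | 82 g | 31.1 g | 31 g |
| Fruit | 129 g | 48.9 g | 49 g |
| Sweetened drinks | 121 mL | 45.8 mL | 47 mL |
| Active time | 30 min | 11.4 min | 12 min |
| Sedentary time | 71 min | 26.9 min | 26 min |

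These figures broadly reproduce with no covariate gain, so the stated power does not depend on the adjustment.

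**3. What adjustment could add**

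The documents give no correlation r between a 3-month parent or home measure and the later child outcome, so r is assumed. Adjustment multiplies residual variance by 1 − r², the detectable difference by √(1 − r²), and the required number by 1 − r². This takes the design effect as unchanged at 1.8. Power is Φ(0.379 × √(111.5/2) / √(1 − r²) − 1.96), with 111.5 effective participants per arm.

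| Assumed r | Variance removed | Vegetables | Active time | Randomised N for the same detectable difference | Power at the unadjusted detectable difference |
|---|---|---|---|---|---|
| 0 | 0% | 31.1 g | 11.4 min | 535 | 80.7% |
| 0.1 | 1% | 30.9 g | 11.3 min | 530 | 81.1% |
| 0.2 | 4% | 30.4 g | 11.1 min | 514 | 82.3% |
| 0.3 | 9% | 29.6 g | 10.8 min | 487 | 84.3% |
| 0.4 | 16% | 28.5 g | 10.4 min | 450 | 87.0% |

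Example at r = 0.4: 223 × 0.84 × 1.8 / 0.75 = 450.

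**The case against.** The strongest reply is that the sentence is correct as naturally read. It qualifies adjustment for baseline values of the outcome. For the child questionnaire and accelerometer outcomes no such value is described, and a parent's diet or activity is a proxy measured in another person. This stands, and it is why the point concerns the breadth of the wording and the covariates left unused rather than a factual error.

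It can also be said that choosing prognostic covariates is commonly left to the analysis plan, and that the sentence speaks of primary outcomes while diet and activity are secondary. Silence would indeed be no finding. Here, however, the article makes a positive statement about diet and activity, and the parenthesis makes sense only if the model is meant to serve those outcomes too.

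Three stronger readings are tempting, and the documents do not support them:

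- *A reader might infer that the plan throws away the 3-month television value.* It does not. The exception names diet and physical activity only, so television viewing stays under the general rule of adjusting where suitable.
- *A reader might infer from Table 2 ("Measures and time-frame for the study") that a sedentary baseline is missing.* That row shows a single tick at 3 months, but in the text available the parent and child lines have lost their alignment, so its owner cannot be read. If it is the child's, table and text agree. No time point is tied to parent television viewing in the text, so the absence of a parent tick would contradict nothing.
- *A reader might infer that chance imbalance in parental behaviour is likely and distorts the comparison.* Sixty groups are randomised, stratified by local government area. Chance imbalance is possible, but it is allowed for in the standard error and is not bias.

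**Conclusion.** The point holds in a limited form. The statement of impossibility is right for the child's own 3-month diet and activity and too broad beyond that. It leaves the secondary child diet and physical activity outcomes without baseline adjustment although prognostic measures are already scheduled.

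The consequence is forgone precision of unknown size: 1% to 16% of residual variance for assumed correlations of 0.1 to 0.4, and none at zero. This rests on the assumed correlations and on an unchanged design effect. It would be wrong to conclude that the trial is underpowered for these outcomes or that its estimates would be biased. The stated detectable differences stand without adjustment, and omitting a covariate does not bias a randomised comparison. The change is worth making because it costs almost nothing, not because the loss is shown to be large.

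**What to change.** In the Statistical analyses section:

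1. Limit the statement of impossibility to the child's own baseline diet and physical activity.
2. Prespecify that child diet outcomes are adjusted for the matching 3-month parent dietary measure, and child physical activity and accelerometer outcomes for 3-month parent physical activity.
3. Confirm that child television viewing is adjusted for the child's own 3-month value.

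The cost is a few lines of wording, settled before outcome data are examined. The measures are already scheduled, so neither data collection nor sample size changes. The one small downside is that some covariate values will be missing, so the plan should say how they are handled to keep those children in the analysis.
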